## Abstract

Climate change is intensifying the frequency and severity of heatwaves, posing growing risks for workers. Home care workers face heightened heat risks due to physically demanding tasks, rising patient needs, frequent travel, and limited access to cooling environments. This study aims to causally evaluate the effectiveness of an app-based intervention (REHEAT strategy) in reducing adverse effects of heatwaves among Swiss home care workers. This multicenter, unblinded, randomized controlled trial (RCT) will involve 350 home care workers from the regions of Northern and Southern Switzerland. Participants will be randomized (1:1) into intervention and control groups, stratified by sex, age group, and geographical location. The intervention group will use the REHEAT app from June to September 2025, while the control group will gain access only after summer 2025. Both groups will be monitored over the summer using a wrist-worn wearable device (smartwatch), online questionnaires, diaries and cognitive tests. The impact of the REHEAT intervention will be evaluated using an Intention-To-Treat (ITT) approach to provide reliable real-world effect estimates, supplemented by Local Average Treatment Effects (LATE) analyses to assess impact based on participant exposure and compliance levels. Primary outcomes include strain accumulation, cognitive performance, emotional distress, sleep, night recovery, and mental and physical health. Outcomes will be analyzed longitudinally with mixed-effects models, while LATE will be estimated using app usage as an instrumental variable in generalized linear mixed models. At the time of submission, recruitment had been successfully completed, with a total of 350 participants enrolled in accordance with the study protocol. The intervention and data collection phases are ongoing, and no outcome data have yet been accessed or analyzed. The findings will inform the development of occupational health interventions in response to heat-related stressors and support climate change adaptation policies for health sector workers.

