**Figure 1. fig1-00469580251405766:**
[figure not shown]
Flow diagram of the REHEAT RCT.

The RCT is implemented from June to September 2025, aligning with the period of highest likelihood for heatwave exposure in Switzerland. Participants in the treatment group receive the REHEAT strategy via a smartphone app, while those in the control group use the same app without active intervention features (only tracking of health- and well-being-related parameters) until the end of data collection in September 2025. Although the study is not blinded, all participants install the app during on-boarding activities, to reduce potential bias. To address the risk of contamination—given that participant from the treatment and control group may work together in the same team and share office spaces—participants are explicitly instructed not to discuss or share app content throughout the duration of the study.

This study design enables a robust estimation of the average treatment effect (ATE), as well as its heterogeneity across subgroups. The evaluation is supported by a longitudinal, multi-source, and multi-method data collection framework, which ensures comprehensive measurement of both outcomes and contextual factors over time. The ATE is estimated during the summer of 2025. In the event that no significant heat events occur during the planned study period, a contingency plan allows for an extension of the trial to the summer of 2026 (June-September 2026).

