Participants in the treatment group receive the REHEAT heat adaptation strategy during Summer 2025 via the REHEAT app, installed on their smartphones. Participants in the control group gain access to the same content only after the summer, in September 2025. As noted previously, group allocation is not blinded. All participants install the study app during on-boarding (June or July 2025); however, only the treatment group has the intervention features activated from the start, while they remain inactive for the control group until the randomized controlled trial ends. Despite limited exposure, there remains some risk of contamination, as participants in both groups work within the same partner organizations and may interact regularly. To reduce this risk, all participants are clearly instructed not to discuss or share the content of the app with colleagues, a condition emphasized as essential to ensure the validity of the study.

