### Intervention

The heat adaptation measures of the REHEAT strategy are co-developed by a multidisciplinary team of experts and stakeholders to tailor previously identified heat adaptation solutions to the specific needs and constraints of home care workers and their organizations. The intervention is designed to be low-burden, fully digital, and seamlessly integrated into daily routines.

The REHEAT app serves as the delivery platform, bringing the tailored measures directly to participants’ smartphones. For participants in the treatment group, the app provides enriched content from initial on-boarding, including practical guides on self-monitoring, hydration, nutrition, clothing and rest, and providing home care workers with app content reminder notifications (once per week), timely heat protection alerts (from 2 days before the heatwave), and local resource maps (Figure 2). In total, the REHEAT strategy covers 4 intervention domains with 12 heat adaptation features.

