Personal Care (6 features). This domain focuses on individual well-being and includes a smartphone-based tool for tracking personal well-being, training materials on recognizing and managing heat-related symptoms, and reminders to check physiological data regularly. It offers expert advice on nutrition and hydration during hot weather, complemented with recipes and reminders of hydration, as well as tips and notifications aimed at improving sleep quality under heat stress.Heat Protection at Work (3 features). This domain provides practical guidance to help workers protect themselves from heat exposure on the job. It includes recommendations for sun protection (sunscreen, sunglasses, hats), advice on selecting and using cooling devices tailored to personal needs, and best practices for managing work clothing, preparing spare garments, and reducing heat exposure in vehicles and air-conditioned environments.Work Activity Planning (1 feature). This domain features a weather alert system integrated in the app, delivering push notifications with heat warnings and standardized advice (eg, “Tomorrow is expected to be hot; plan your breaks and bring sufficient water and fruit”). Unlike other services, these alerts will appear even if the app is closed or running in the background.Refreshment and Leisure Time (2 features). These domains improve access to local resources for breaks at work and for leisure. An interactive, geo-located map highlights designated rest areas such as parks, cafes, shops, and libraries that offer sanitary facilities or access to potable water. Additional alerts provide information on nearby leisure facilities such as swimming pools and gyms, including opening hours and special offers through local partnerships.

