### Statistical Analysis Plan

The evaluation of the REHEAT heat adaptation strategy consider the following 4 areas: implementation and compliance, impact, heterogeneity, and satisfaction.

Implementation and compliance: descriptive statistics and inferential comparisons assess baseline equivalence between treatment and control group and participant compliance across relevant sociodemographic characteristics, work experience, health condition, and selected outcomes. App usage data is analyzed using frequency distributions and stratified analyses by age, sex, and location to ascertain user engagement with the app.Impact Analysis: The impact of the REHEAT strategy is first evaluated using an Intention-To-Treat (ITT) approach, which yields the most reliable estimates for real-world interventions by preserving the benefits of randomization. In parallel, Local Average Treatment Effects (LATE) are estimated to assess the intervention’s effects at varying levels of participants’ potential heat exposure and compliance. ITT analyses are conducted at the individual level. The effects of REHEAT on the primary outcomes—measured at on-boarding and off-boarding—as well as on those monitored throughout the summer, are estimated using random-intercept mixed-effects models. By accounting for within-subject correlations over time, this approach supports a robust analysis of longitudinal data. LATE estimates on primary outcomes are derived using instrumental variable generalized linear mixed models (IV-GLMM), with MeteoSwiss weather data and REHEAT app usage serving as instruments. Specifically, passively recorded data on the frequency of use of the app’s features over time are used as a proxy for participants’ compliance with the intervention. These models control for randomization strata and blocks, as well as a set of time-invariant and time-varying co-variates deemed theoretically or empirically relevant. Because heat effects vary across time, cumulative exposure, and acclimatization,^57,58^ temporal factors are explicitly controlled in the analyses. Exposure to heat is modeled using distributed lag models to capture both immediate and delayed effects of temperature and humidex across pre-specified lag periods. Mixed-effects models include calendar-week splines, random slopes for time, and adjustments for survey date and recent mean temperature to account for differences in measurement timing and seasonal acclimatization.^
59

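### The supplementary LATE analysis names app usage and weather as instruments and omits the randomised arm, so its estimates are open to self-selection bias; the ITT analysis is unaffected.

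*Protocol article*

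**What the plan says.** In the Statistical Analysis Plan (Impact Analysis), impact is evaluated first by ITT. LATE is estimated in parallel on the primary outcomes with instrumental-variable generalized linear mixed models, "with MeteoSwiss weather data and REHEAT app usage serving as instruments". The Abstract, which presents LATE as a supplement to ITT, says the same of usage: "LATE will be estimated using app usage as an instrumental variable in generalized linear mixed models".

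The sentence after the first quote gives usage a different role: logged frequencies of use of the app's "features over time are used as a proxy for" participants' compliance. Randomisation enters the LATE models only through its design factors: "These models control for randomization strata and blocks". The arm is not named as an instrument anywhere in the article.

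The same paragraph models temperature and humidex with distributed lags as exposures acting on the outcomes, and adjusts the mixed models for recent mean temperature. The Effect Heterogeneity paragraph carries LATE into the moderation models by sex, age, region and time.

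On access, Randomization and Allocation states that "only the treatment group has the intervention features activated from the start", and that these features stay inactive for controls until the trial ends.

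**The concern.** An instrument must shift the treatment received, share no cause with the outcome, and affect the outcome only through that treatment. The two named instruments fail on different counts.

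- **App usage** is the treatment received. Participants choose it after allocation. Health-conscious workers may open the app more, and so may workers who are already suffering from the heat. Either habit links usage to the outcome without any effect of REHEAT, and the two push the estimate in opposite directions.
- **Weather** changes strain, sleep and recovery directly; that is why the trial exists. For the effect of REHEAT it breaks the exclusion condition.

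At stake is the plan's only compliance-based effect estimate. It covers the primary outcomes, is announced in the Abstract and would be reported as causal. As written it has the self-selection bias of an as-treated comparison.

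**Working it through.** **No published figure to reproduce.** The article reports no LATE calculation. Its one design figure is the sample size, about 330 to 370, given without σ or Δ. For scale only, its formula can be solved backwards with α = 0.05 two-sided and 80% power: d = (1.960 + 0.842) × √(2/n per arm).

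- 330 in total (165 per arm): d = 0.308
- 350 in total (175 per arm): d = 0.300
- 370 in total (185 per arm): d = 0.291

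**Bias with usage as instrument.** From the documents: 350 participants, 1:1 allocation. Assumed: no effect of REHEAT; outcome SD 1; usage zero in controls and log-normal in the treated arm, with mean m and log-SD s; correlation ρ between log-usage and outcome. Linear two-stage least squares stands in for the mixed model.

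With usage Z as instrument for being treated, D:

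- cov(Z, D) = m/2 − (m/2)(1/2) = m/4
- cov(Z, Y) = (1/2) × ρ × s × m
- spurious effect = cov(Z, Y) / cov(Z, D) = 2 × ρ × s

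A coefficient of variation (CV) of 1 gives s = √(ln 2) = 0.83; a CV of 0.53 gives s = 0.5; a CV of 0.31 gives s = 0.30. Spurious effect in SD from the formula, with simulated rejection rate at nominal 5%:

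| Usage CV (log-SD) | ρ = 0.1 | ρ = 0.2 | ρ = 0.3 |
|---|---|---|---|
| 0.31 (0.30) | 0.06; 9% | 0.12; 18% | 0.18; 33% |
| 0.53 (0.50) | 0.10; 11–13% | 0.20; 31–35% | 0.30; 60–62% |
| 1.00 (0.83) | 0.17; 14% | 0.33; 41% | 0.50; 76% |

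The two values in the middle row come from separate runs of 4,000 and 1,000 replicates. At ρ = 0 (log-SD 0.5) rejection is 5.1%: no inflation.

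**Usage as its own instrument.** The model is then an as-treated regression. Rejection is 5.5%, 12.7%, 36.7% and 63.9% for ρ = 0, 0.1, 0.2 and 0.3 (log-SD 0.5).

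**Weather as instrument for usage.** This used 300 runs of daily data, 30 days per person. Heat was assumed to lower the outcome by 0.2 per SD of temperature and to raise usage through alerts. A true null was rejected in 100% of runs at every ρ, with a mean estimate of about −0.58 to −0.59 per unit of use, that is, apparent harm. With the direct heat effect set to zero (ρ = 0.2), rejection was 4.3%. The direct path is the whole problem.

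**Arm as instrument for usage.** Person-level rejection was 5.7%, 5.1%, 5.6% and 4.5% for ρ = 0 to 0.3, with a mean estimate of about 0. The smaller daily runs varied from 2.7% to 9.0% and averaged 5.3%. This estimate is per unit of use, so it is comparable with the table on error rate but not on effect size.

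**The case against.** The strongest defence is that the wording is loose. The compliance sentence gives usage the role of the endogenous variable, so the authors may have meant the arm as an unstated instrument. That is possible, but the Abstract and the Methods both call usage the instrument, so the text needs correcting on either reading.

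Weather can also be defended in part. The plan says LATE is to cover levels of potential heat exposure as well as compliance, and the Discussion concedes that actual exposure is not measured. Weather may be meant as an instrument for actual exposure, and acting through heat is then no violation in itself. That analysis would estimate an effect of heat, however, not of REHEAT, and the plan does not say which instrument belongs to which endogenous variable.

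The numbers are illustrative. They depend on an assumed correlation and usage spread, and on a model in which usage instruments being treated, which the article does not spell out. This stands, and it is why a range is shown.

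A reader might infer that control usage is certainly non-zero. The Personal Care domain "includes a smartphone-based tool for tracking personal well-being", while Trial Design gives controls "only tracking of health- and well-being-related parameters". Whether these are the same function depends on Figure 2, which is not available here, so the overlap is a point to check and not a finding.

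**Conclusion.** The stated specification is wrong as written; this is not detail left to another document. Usage is self-selected treatment received, weather has an acknowledged direct path to the outcomes, and the randomised arm is not named. These points follow from the text and need no simulation.

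The size is conditional. For correlations of 0.1, 0.2 and 0.3, spurious effects are about 0.10 to 0.17, 0.20 to 0.33 and 0.30 to 0.50 SD at log-SD 0.5 to 0.83, and smaller when usage varies less. At the higher correlations they are comparable with the 0.29 to 0.31 SD implied by the sample size. That benchmark is back-solved and must not be read as the trial's stated planned effect.

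A reader might go further and infer that the trial's main conclusion is compromised, or that a false effect will appear. Neither is supported. ITT comes first and uses none of these instruments, and zero correlation produces no inflation from usage. The fault is a risk of bias confined to the supplementary LATE estimates and their moderation models.

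**What to change.** In the Impact Analysis paragraph, replace the instrument sentence with a statement to this effect:

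- The randomised arm is the instrument. Where the effect is allowed to vary with heat, arm by pre-specified heat exposure is added, with the weather main effects in the model.
- The endogenous variable is logged use of the intervention features, excluding any tracking function also active in controls, to be checked against Figure 2.
- MeteoSwiss data enter as covariates or effect modifiers, not as instruments.

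Correct the Abstract to match, and apply the same specification to the LATE moderation models. Treat contamination reported at off-boarding as a sensitivity analysis, since questionnaire items and logged frequencies have no common scale. The choice of instrumental-variable estimator can stay with the analysts.

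One assumption should be stated alongside: heat alerts appear even when the app is closed, so the usage measure should either count delivered alerts or the authors should argue that the arm acts only through the logged use.

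The cost is wording; the data and software are the same. The price is wider confidence intervals for the LATE. At submission no outcome data had been accessed, and the change is most credible if dated before they are.

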### Randomization and Allocation

Randomization is carried out using a 1:1 allocation ratio through a computer-generated sequence, employing stratified block randomization to ensure balance between key co-variates.

Block randomization within strata works by first dividing participants into homogeneous subgroups (ie, strata) based on key baseline co-variates (eg, age). Within each stratum, participants are then randomized in small, fixed-size blocks to ensure that each treatment group is equally represented in every block. This dual-layered approach helps to maintain overall balance in treatment allocation across important co-variates (through stratification) while also preventing accidental imbalances due to random chance within each stratum (through blocking). It is particularly effective with a limited number of relevant predictors and in samples of small to moderate size, where simple randomization may lead to imbalance.^
44
^ In our case, we opted for stratification by age (<50 years vs ≥50 years), sex (male vs female), and geographical area (Southern vs North-Eastern Switzerland), and use blocks of 4 to ensure consistent treatment balance within each stratum.

The random allocation sequence is generated by the investigator overseeing the Ticino study site, without involvement from external personnel. Randomization is conducted after the completion of participant recruitment and immediately prior to onboarding and initiation of the intervention phase. Because randomization occurs only after recruitment is finalized, no ongoing allocation sequence requires concealment, eliminating the potential for selection bias due to prior knowledge of group assignments.

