Sleep quality & quantity	Sleep and recovery	Garmin smartwatch; app-based questionnaires; pre- and post-intervention questionnaires	Daily, with a focus on baseline vs heatwaves occurrence; Middle term, pre- and post-intervention	Objective sleep duration and circadian rhythm; self-reported sleep quality and duration (B-PSQI, Karolinska sleep diary)^51,52^
Nighttime recovery	Physiological recovery	Garmin smartwatch; app-based questionnaires	Daily, with a focus on baseline vs heatwaves occurrence	Objective physiological heart rate metrics; self-reported recovery (Karolinska sleep diary)^ 51 ^
Mental & Physical Health	General health	App-based questionnaires; pre- and post intervention questionnaires	Daily, with a focus on baseline vs heatwaves occurrence; middle term, pre- and post-intervention	Self-reported injuries, general health, mental health (MHI-5),^53,54^ burnout (SMBM)^ 55 ^
*Secondary outcomes*				
Intervention Compliance	Engagement	App usage logs	Continuously during intervention	App interaction frequency and feature use tracked via in-app activity logs
Manipulation check	Health behavior	Garmin smartwatch; app-based questionnaires	Daily, with a focus on baseline vs heatwaves occurrence	Self-reported and objective indicators of coping behaviors for hydration, nutrition, peak-hour strenuous activity, etc.
User satisfaction & experience	User Experience	post-intervention questionnaire; interviews with subsample	Post-intervention	user experience questionnaire and qualitative interviews

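### The models are to control for randomization blocks of 4 (88 to 93 blocks for 350 people) without saying how; if blocks enter as fixed terms, error rates and sparse yes/no estimates would suffer

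*Protocol article*

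**What the plan says.** In the protocol article, Statistical Analysis Plan (Impact Analysis), the intention-to-treat effects "are estimated using random-intercept mixed-effects models". The text then turns to the local average treatment effects: "LATE estimates on primary outcomes are derived using instrumental variable generalized linear mixed models (IV-GLMM"). Shortly after that comes the covariate statement: "These models control for randomization strata and blocks", together with further time-invariant and time-varying covariates. Nothing says whether blocks are fixed or random, or whether the statement reaches back to the intention-to-treat models.

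Randomization and Allocation sets the design. "Randomization is carried out using a 1:1 allocation ratio", with "stratification by age (<50 years vs ≥50 years), sex (male vs female), and geographical area (Southern vs North-Eastern Switzerland"). The investigators "use blocks of 4 to ensure consistent treatment balance within each stratum". On timing: "Randomization is conducted after the completion of participant recruitment and immediately prior to onboarding and initiation of the intervention phase". The Results section reports 350 people enrolled.

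Table 1 (Outcomes) places "Self-reported injuries, general health, mental health (MHI-5") and burnout within one primary outcome, collected daily and before and after the intervention. It does not give a response format for injuries.

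**The concern.** Blocks of 4 are a device for keeping the arms balanced. Here the whole list is randomized at once after recruitment, so block membership need not mark calendar time of accrual, and nothing in the article ties it to site or team. Beyond the stratum, a block may be little more than an arbitrary group of four people.

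Giving each such group its own free parameter uses about one between-person term per four people. In a logistic model with few records per person this is the incidental-parameter problem: the odds ratio is pushed away from 1 and the test is too liberal. In a mixed model fitted by maximum likelihood, the between-person variance is underestimated because the likelihood makes no allowance for the terms spent, so standard errors are too small. In linear models, a block that loses both members of one arm contributes nothing to the treatment contrast. At stake are the type I error rate and, for sparse yes/no outcomes, the size of the reported effect.

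**Working it through.** **Inputs from the article.** 350 enrolled (Results); block size 4, 1:1 allocation and 2 × 2 × 2 = 8 strata (Randomization and Allocation); two-sided alpha 0.05, 80% power and a target of about 330 to 370 (Sample Size Calculation).

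**The plan's own figure.** The article states no block count, and gives no values for the standard deviation or the expected difference, so its sample size cannot be reproduced forward. Solving its formula backwards with 165 per arm: d = (1.960 + 0.842) × √(2/165) = 0.308. The range fits a margin of about 10%: 330 × 1.10 = 363 and 330/0.9 = 367, against 370. I use d = 0.308 below as an assumption.

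**Block count.** The minimum is 350/4 = 87.5, so 88. Part-filled last blocks in up to 8 strata raise this to at most 93. Fixed coding therefore needs 87 to 92 block terms, against 7 for strata.

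**(a) Yes/no outcome, logistic model.** Simulation with 350 people, 8 strata of assumed sizes and one record per person:

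| Control risk | True log OR | Mean, fixed blocks | Mean, strata only | Mean, conditional on block |
|---|---|---|---|---|
| 20% | -0.693 | -0.927 | -0.711 | -0.693 |
| 30% | -0.511 | -0.680 | -0.513 | -0.507 |

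The ratios are 0.927/0.693 = 1.34 and 0.680/0.511 = 1.33. Under the null (4,000 runs each), type I error with fixed blocks is 8.7% at 10% risk and 8.9% at 30% risk, against 4.7% and 5.4% with strata only.

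With repeated records per person (assumed independent, 88 blocks, true log OR -0.511), the overstatement fades. The ratio of mean estimate to truth is 1.32 to 1.34 with one record, 1.13 to 1.17 with two, 1.04 to 1.11 with five, and 1.00 to 1.02 from ten upward.

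**(b) Mixed models fitted by maximum likelihood.** Take 88 full blocks, so 352 people, with equal numbers of records. Fixed blocks plus treatment use 89 between-person terms; strata plus treatment use 9. Maximum likelihood estimates the between-person variance of participant means too low by the factor (352 − p)/352, so a nominal 1.96 test in fact uses the cut-off 1.96 × √((352 − p)/352) on a t distribution with 352 − p degrees of freedom.

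- Fixed blocks: 263/352 = 0.747, cut-off 1.694, type I error 9.1%.
- Strata only: 343/352 = 0.974, cut-off 1.935, type I error 5.4%.

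REML divides by 352 − p and removes the problem in linear models.

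A logistic mixed model behaves similarly. With 30 records per person, 20% baseline risk, participant SD 1 and 400 simulations (all assumed), fixed blocks left the estimate unbiased, but the mean standard error was 0.104 against an actual SD of 0.122, and type I error was 9.5%. With strata only it was 6.3%. With 400 runs the Monte Carlo standard error near 9.5% is √(0.095 × 0.905/400) = 1.5 points.

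**(c) Continuous outcome, one value per person, d = 0.308.** Information on treatment is proportional to the sum of n1·n0/(n1 + n0) over blocks, or over strata. Complete 2:2 blocks are orthogonal to treatment. Residual degrees of freedom fall from 341 to between 256 and 261, which moves the critical t only from 1.967 to 1.969.

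| Dropout | Information kept, blocks vs strata | Power, strata | Power, blocks | Loss (points) |
|---|---|---|---|---|
| 0% | 99% | 82.0% | 81.5% | 0.5 |
| 10% | 95% | 77.6% | 75.6% | 2.0 |
| 20% | 91% | 72.5% | 68.3% | 4.2 |
| 30% | 86% | 66.5% | 59.7% | 6.8 |

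**The case against.** The strongest reply is that the harmful model is not the one written down. The article says only that blocks are controlled for. In a paragraph about mixed models a block random intercept is a natural reading, and how a block term enters is the kind of detail often left to a fuller analysis plan. The sentence follows the instrumental-variable text, so it may not touch the intention-to-treat models at all. These points stand, and they make the harm conditional.

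A reader might infer that the plan will overstate the effect on injuries by a third. The article does not support that. It gives no response format for injuries, collects them daily as well as before and after, and elsewhere in the section describes the multilevel outcomes as continuous and repeatedly measured. The overstatement needs fixed terms, a yes/no response and very few records per person. The error-rate problem in (b) is wider: it persists with 30 records per person. It still needs fixed terms, and in linear models it needs maximum likelihood rather than REML.

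A reader might also infer that blocks can carry no prognostic information. That goes too far. The article does not say how people were ordered before blocks were filled. Consent meetings were held organization by organization and onboarding ran over June and July, so a list sorted by organization or sign-up could make blocks mildly informative.

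Nor is the nesting of blocks in strata a defect: software drops the redundant columns and the treatment estimate is unchanged.

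Finally, the power loss in (c) is small, and the calculation treats a person as wholly present or wholly lost. Repeated measures and the planned multiple imputation would soften it.

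**Conclusion.** The point holds in conditional form. The article does commit its models to adjusting for 88 to 93 blocks of four, and leaves open both the form of the term and the models concerned. A random block intercept would do little harm. Fixed block terms would raise type I error from about 5% to roughly 9%, either in maximum-likelihood mixed models or in a single-record logistic model. They would overstate the log odds ratio by about one third only when a yes/no outcome has one record per person. For continuous outcomes the power cost is minor unless dropout reaches 20 to 30%.

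These sizes rest on assumed stratum sizes, event risks of 10 to 30%, odds ratios of 0.5 to 0.6, d = 0.308, dropout at random, and independent records in the repeated-record runs of (a). The instrumental-variable mixed model itself was not simulated. The change is worth making because it costs almost nothing: it is no worse in substance if blocks were meant as random, and clearly better if they were meant as fixed.

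**What to change.** In the Impact Analysis paragraph, replace the adjustment for strata and blocks by adjustment for the three stratification factors (age group, sex, region) as fixed terms, and drop the block. If the block is kept, for example because the list order followed organization or sign-up, state that it enters only as a random intercept, never as fixed terms. Say whether the sentence applies to the intention-to-treat models, the instrumental-variable models or both.

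The change is a few words. Balance between arms is untouched, since the design has already secured it within strata. The only downside is a small possible loss of precision if blocks do carry prognostic information. The Results section states that no outcome data had been accessed at submission, so a change made at that stage would have been free of hindsight.
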